#### Comparison

In designing the control condition, our intention was to provide a more active condition than simply (re)training as usual. Given that clinicians have already trained in PCIT previously, we were mindful of enhancing the content so as to make participation worthwhile for clinicians and to justify the costs associated with replicating the training. As such, and as outlined in ‘All participants’ above, participants in the control condition will receive enhanced refresher training, which includes problem-solving and facilitated planning and implementation discussions, along with basic resources to aid implementation, such as ECBI questionnaires. They will also receive optional complimentary weekly PCIT-oriented consultation.

Figure 1 represents the CONSORT flow diagram, and the CONSORT checklist is provided as an Additional file [35].

**Fig. 1 Fig1:**
[figure not shown]
CONSORT flow diagram

### Outcomes and measures

Baseline data will be collected from all participants, via a Qualtrics survey prior to allocation being revealed. The re-implementation intervention will be available for a period of 6 months to the intervention group. Some aspects of the re-implementation intervention occur at one point in time (e.g. the refresher training) and others continue across the trial period (e.g. access to equipment and co-worker, consultation). All aspects of the intervention will be contained within a 6-month period and will cease at that point. Table 2 provides a summary of outcomes and measures.

**Table 2 Tab2:** Summary of outcomes, measures and time points

		**0**	**1**		**2**		**3**	
**Method**		**Pre-trial information session**	**Baseline (beginning of day 1 of refresher training)**		**Monthly throughout trial (begins 1-month post-randomisation)**		**End of trial (6 months post randomisation)**	
			**Control**	**Intervention**	**Control**	**Intervention**	**Control**	**Intervention**
**Acceptability of trial processes and data collection methods**								
Study-specific Qualtrics questionnaire	Acceptability of trial processes (incl. to those choosing not to enrol)	X					X	X
	Number of participants enrolled in trial	X						
	Number of participants completing trial						X	X
	Response rates to study questionnaires				X	X		
	Test of blinding						X	X
**General data**								
Study-specific Qualtrics questionnaire	Age and gender		X	X				
	Ethnicity		X	X				
	Professional discipline		X	X				
	Service/setting characteristics		X	X				
	Role characteristics (e.g. other demands, FTE worked)		X	X				
	Professional development activities (e.g. training and supervision) undertaken in six month trial period – in addition to trial intervention components						X	X
**Adoption**								
Study-specific Qualtrics questionnaire	Number of families provided with PCIT in past 1 week		X	X	X	X	X	X
**Implementation determinants**								
Theoretical Domains Framework Questionnaire [36] (via Qualtrics)	61 items, 7-point Likert scales		X	X			X	X
Capability, Opportunity, Motivation to use PCIT (based on [37]) (via Qualtrics)	3 items, 10-point Likert scales				X	X		

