### Study aims

The primary objective of this pilot study is to assess the feasibility of conducting a RCT. In the future, this fully powered RCT will assess the effects of the provision of a re-implementation intervention on the adoption of PCIT by clinicians who are not—or are rarely—using PCIT in their practice. The current feasibility trial will identify any factors that may detract from our ability to achieve this aim in the full trial.

This trial aims the following:Pilot the recruitment and trial procedures to assess recruitment rates, assess the characteristics of clinicians who enrol in the trial, assess whether the idea of randomisation is acceptable to participants.Identify any specific cultural factors that may influence recruitment, data collection methods or sampling frameworks and determine the acceptability of the reimplementation intervention for Māori participants.Assess the acceptability of the re-implementation package to clinician participants, in order to refine the components of the PCIT re-implementation intervention.Pilot the use of a series of online self-report surveys as a data collection method for assessing the effects of the re-implementation intervention on clinician capability, opportunity and motivation.Explore potential effects of the PCIT re-implementation intervention on clinician adoption of PCIT. This will include identifying the variability of the proposed primary outcome variable at the end of the intervention, to calculate an appropriate sample size for a definitive RCT.

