#### Randomisation and blinding strategies

All participants will have been recruited and will have participated in the two refresher training days (refer ‘Study Treatments’, below) prior to random allocation to intervention and control groups. Allocation to groups will occur at the end of the second day of refresher training. A random allocation sequence will have been generated by the study statistician (using a simple 1:1 randomisation with no restrictions), who will contact participants via email with their group allocation. Participants will be asked not to share the email or reveal or discuss the condition to which they have been allocated. We will undertake a test of blinding at the end of the intervention (i.e. will ask participants which condition they believed themselves to have been allocated) in order to determine whether blinding is feasible in a future trial.

The first author will be delivering some of the re-implementation supports and will therefore be unable to be blinded. The remainder of the research team, particularly outcome assessors, will be blinded.

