#### Secondary outcomes

Acceptability of trial processes to participants will be measured by a study-specific survey following the pre-trial information session and at the end of the trial. Those who choose *not* to enrol in the trial following the information session will also be asked to complete the study-specific survey as to their reasons for non-participation, and a frequency count of responses to these multiple-choice items will be undertaken.

Clinician self-reported Capability, Opportunity and Motivation to use PCIT (drawn from COM-B theory; [23]) will be measured by Likert scale items within a monthly self-report survey, developed for the purposes of this trial and delivered via Qualtrics.

Acceptability of the monthly surveys as a data collection method, and the timing and frequency of these, will be measured by response rates. Also, a post-trial semi-structured phone interview will incorporate Likert scales and seek participants’ ratings of the acceptability of the monthly surveys as a data collection method.

Acceptability of each aspect of the re-implementation intervention will be assessed by participant uptake of the components. As an online booking system will be used to coordinate the loan of (1) the audio-visual equipment, (2) the time-out cubicle and (3) the mobile co-worker, a frequency count of weekly bookings will be used as a proxy measure for the acceptability of these items.

Also, in a post-trial semi-structured phone interview, participating clinicians will be asked to rate the acceptability of the components of the re-implementation package on a series of Likert scales. Acceptability of group consultation sessions will be assessed by participant attendance rates, measured by an audit of session attendance registers.

Clinician adoption of PCIT will be assessed by clinician self-report of the number of unique families to whom PCIT was delivered in the most recent representative 1-week period at 6 months post-randomisation and compared to baseline (via the study-specific monthly survey). Given that PCIT sessions are typically held weekly, this is expected to provide a valid measure of clinician PCIT adoption.

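### The three capability, opportunity and motivation items are not asked before allocation, so change from baseline on them cannot be described

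*Protocol article*

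**What the plan says.** Under Implementation determinants, Table 2 of the protocol article lists two measures. The TDF Questionnaire ("61 items, 7-point Likert scales") is marked at baseline and at the end of the trial. The COM measure ("3 items, 10-point Likert scales") is marked only in the two monthly columns, headed "Monthly throughout trial (begins 1-month post-randomisation"; its baseline and end-of-trial cells are empty. The baseline column is headed "Baseline (beginning of day 1 of refresher training", which is before both training and allocation.

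The Secondary outcomes section agrees with the table: the COM constructs "will be measured by Likert scale items within a monthly self-report survey". The fourth aim is to pilot the online surveys as a method for "assessing the effects of the re-implementation intervention on clinician capability, opportunity and motivation".

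Allocation is made at the end of the second training day, "using a simple 1:1 randomisation with no restrictions". The supports are available from then on. The planned size is 10 clinicians per arm. Statistical methods plans mainly descriptive summaries, names only adoption for exploratory testing, and says that baseline differences will be noted but not adjusted for.

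**The concern.** The measure is being piloted as a way to detect effects on capability, opportunity and motivation, which the Background treats as the route by which the supports act. Its first reading comes after exposure has begun in both arms: the refresher training for everyone, and about a month of supports for the intervention arm. A later score cannot be set against where a clinician started on the same items.

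This limits what the pilot can teach. It cannot show how far the short measure moves from a pre-exposure level, or how strongly that level predicts later scores. Both would help in deciding how to use the measure in the definitive trial. An analysis plan cannot repair this later, because the values will not have been collected.

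**Working it through.** **Schedule check.** The three relevant rows of Table 2, read cell by cell (each mark applies to both arms):

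| Measure | Baseline | Monthly | End of trial |
|---|---|---|---|
| Adoption (families in past week) | X | X | X |
| TDF Questionnaire | X | – | X |
| COM items | – | X | – |

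The neighbouring rows read cleanly and the text places the COM items in the monthly survey, so the empty cells are not an artefact of text extraction. No other section schedules these items before allocation.

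**What cannot be estimated.** The following need a pre-exposure score on the same items: change from baseline within clinician, baseline balance on the items, and the baseline-to-follow-up correlation (rho). Change between month 1 and later months can still be described.

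**Precision.** The plan states no figure here to reproduce. Inputs: 10 per arm (Sample size and justification); rho is not given, so it is assumed over 0.3 to 0.7. Differences are in units of the between-clinician standard deviation (SD), taken as equal in the two arms.

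- Standard error (SE) of a follow-up-only difference: sqrt(1/10 + 1/10) = sqrt(0.2) = 0.447 SD.
- SE after adjustment for own baseline: 0.447 × sqrt(1 − rho²).
- Variance of a simple change-score comparison, relative to follow-up only: 2(1 − rho).

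| Assumed rho | sqrt(1 − rho²) | Adjusted SE | CI shorter by | Relative variance, change score |
|---|---|---|---|---|
| 0.3 | 0.954 | 0.427 SD | about 5% | 1.4 |
| 0.5 | 0.866 | 0.387 SD | about 13% | 1.0 |
| 0.7 | 0.714 | 0.319 SD | about 29% | 0.6 |

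These are large-sample factors; with about 20 clinicians, estimating the slope gives back a little of the gain. The last column shows that a comparison of raw change scores is less precise than follow-up only at rho 0.3 and no better at 0.5. Change scores are therefore useful mainly for description.

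**Chance imbalance, for scale.** The probability that the arms differ by more than 0.5 SD at baseline on any one item is 2 × (1 − Φ(0.5/0.447)) = 0.26. This applies to any variable with 10 per arm. For the COM items such a difference could not be seen.

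**The case against.** The strongest reply is that no planned analysis is harmed. The fourth aim pilots the surveys as a collection method, their acceptability is judged by response rates and interviews, and the progression criterion is an 80% average response rate. No section promises a change-from-baseline or adjusted COM analysis. A long instrument at baseline and end with a short tracker between is a coherent design. This stands, and it keeps the point small. But even a descriptive account of change needs a starting value.

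Four stronger readings are tempting, and the document does not support them:

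- **That a difference at months 1 to 6 could not be told from a pre-existing one.** Allocation is random, so the follow-up comparison is unbiased in expectation. Chance imbalance is already contained in the SE of 0.447 SD; the 26% is not an added error.
- **That nothing is known about these constructs at baseline.** The TDF Questionnaire is taken before allocation, and the Background says its domains map onto the three COM factors. It can serve as an indirect check on imbalance or as a proxy covariate, neither of which needs a common scale. It cannot give change on the three items themselves.
- **That some item is more likely than not to be imbalanced.** Multiplying over three items gives 1 − (1 − 0.264)³ = 0.60, but only if the items are independent. The logic model links them, and positive correlation would lower the figure.
- **That the six-month COM score is also missing.** A monthly survey starting at month 1 of a six-month trial should reach month 6, and Secondary outcomes takes the six-month adoption count through the monthly survey. The empty end-of-trial cell probably loses nothing.

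**Conclusion.** The gap is real and narrow. The COM items have no pre-allocation value, so within-clinician change from baseline, baseline balance and the baseline-to-follow-up correlation cannot be obtained for them. The cost in precision is about 5%, 13% or 29% of confidence-interval width at rho 0.3, 0.5 or 0.7; these correlations are assumed, and nothing in the document favours the upper end for single items.

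The validity of the randomised comparison is not at stake, and neither are the primary feasibility outcomes or the progression criteria. Sample-size planning for the definitive trial is expected to rest on adoption, which does have a baseline, so the missing correlation matters for planning the use of the COM measure only. This is an optional improvement, worth making because it is cheap and cannot be made once training has begun.

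**What to change.** 1. In Table 2, mark the COM items at baseline in both arms and add them, worded as in the monthly survey, to the baseline Qualtrics survey given at the start of the first training day.
2. Describe monthly scores and change from baseline by arm. Change will include the effect of the refresher training, which both arms receive, so only the contrast between arms bears on the supports.
3. Label any baseline-adjusted estimate as exploratory, and word Statistical methods to allow for it, since that section now rules out accounting for baseline differences. Report the observed baseline-to-follow-up correlation with its confidence interval, which will be wide with about 20 clinicians.
4. Confirm that the month-6 monthly survey carries the COM items. A separate end-of-trial administration is then unnecessary.

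The cost is three more Likert items in a survey that already carries 61 TDF items, plus an edit to Table 2 and a sentence in Statistical methods.

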**Acceptability of intervention components**								
Online booking system data	Usage of audio-visual equipment, time-out tents, co-worker					X (weekly)		
	Attendance at group consultation sessions				X (weekly)	X (weekly)		
Semi-structured interviews							X	X

#### Primary outcome

The primary objective of this pilot study is to assess the feasibility of conducting a RCT. In future, this fully powered RCT will assess the effects of the provision of a re-implementation intervention on the adoption of PCIT by clinicians who are not—or are rarely—using PCIT in their practice. The current feasibility trial will identify any factors that may detract from our ability to achieve this aim in the full trial. Primary outcomes are (1) the number of clinicians who enrol in the trial and (2) the number of clinicians who complete the trial.(1) Recruitment processes will be evaluated by assessing the number of clinicians who provide consent to participate in the trial—this will be determined by an audit of study enrolment logs at baseline (beginning of day 1 of PCIT refresher training).(2) Trial procedures will be evaluated by assessing the number of clinicians who complete the trial, as determined by an audit of study logs at the end of the trial (6 months post-randomisation). When a clinician withdraws from the study, the point of withdrawal and reason for withdrawal will be recorded.

#### Secondary outcomes

Acceptability of trial processes to participants will be measured by a study-specific survey following the pre-trial information session and at the end of the trial. Those who choose *not* to enrol in the trial following the information session will also be asked to complete the study-specific survey as to their reasons for non-participation, and a frequency count of responses to these multiple-choice items will be undertaken.

Clinician self-reported Capability, Opportunity and Motivation to use PCIT (drawn from COM-B theory; [23]) will be measured by Likert scale items within a monthly self-report survey, developed for the purposes of this trial and delivered via Qualtrics.

Acceptability of the monthly surveys as a data collection method, and the timing and frequency of these, will be measured by response rates. Also, a post-trial semi-structured phone interview will incorporate Likert scales and seek participants’ ratings of the acceptability of the monthly surveys as a data collection method.

Acceptability of each aspect of the re-implementation intervention will be assessed by participant uptake of the components. As an online booking system will be used to coordinate the loan of (1) the audio-visual equipment, (2) the time-out cubicle and (3) the mobile co-worker, a frequency count of weekly bookings will be used as a proxy measure for the acceptability of these items.

Also, in a post-trial semi-structured phone interview, participating clinicians will be asked to rate the acceptability of the components of the re-implementation package on a series of Likert scales. Acceptability of group consultation sessions will be assessed by participant attendance rates, measured by an audit of session attendance registers.

Clinician adoption of PCIT will be assessed by clinician self-report of the number of unique families to whom PCIT was delivered in the most recent representative 1-week period at 6 months post-randomisation and compared to baseline (via the study-specific monthly survey). Given that PCIT sessions are typically held weekly, this is expected to provide a valid measure of clinician PCIT adoption.

Acceptability of the recruitment and trial processes to Māori clinicians will be assessed by multiple-choice items within a study-specific questionnaire following the pre-trial information session and at the end of the trial. Māori clinicians choosing not to enrol in the trial will also be offered the opportunity to speak kanohi-ki-te-kanohi (face to face) or via phone with a Māori research team member, to discuss their impressions and any concerns about trial recruitment processes and/or methodology that contributed to their decision not to participate, and this qualitative data will be recorded.

### Statistical considerations

#### Sample size and justification

As this is a feasibility study, sample size calculations are not required, and a formal power calculation is not appropriate, given that the primary outcome for this pilot is feasibility [38]. Instead, sample sizes for feasibility studies should be based on pragmatic considerations [39]. However, for the RCT, it is envisaged that the primary outcome will be *adoption*: clinician self-report of the number of unique families to whom PCIT was delivered in the most recent representative 1-week period at 6 months post-randomisation, compared to baseline. These data will be collected.

Relevant pragmatic considerations included the size of the group of PCIT-trained clinicians thought to be practicing in the Tāmaki Makaurau/Auckland region, excluding the research team (approximately 70). Also, the budget for the research project will only support limited co-worker hours, and the purchase of limited time-out pop-up cubicles and limited audio-visual equipment and toy packages. Given these practical constraints, we hope to recruit 10 participants per condition or 20 overall. We are interested in evaluating whether the proposed recruitment methods will be effective in a future, larger trial. While we will aim to recruit this number, our ability to do so will provide valuable data around our ability to recruit sufficient participants for a fully powered trial using the described methods.

#### Progression criteria

The following criteria will be used to assess whether it is feasible to progress to a fully powered randomised controlled trial in the future.Clinician recruitment rate: study is considered feasible if at least 20 clinicians enrol in the trial. Given that we have contact information for 70 PCIT-trained clinicians in the region (i.e. the population of interest), we consider this number to be reasonable.Clinician trial completion rate: study is considered feasible if there is a maximum of 20% attrition.Acceptability of surveys as a data collection method: study is considered feasible if the average survey response rate (across the baseline, monthly and end-of-trial surveys) is at least 80%.

#### Statistical methods

The purpose of pilot studies is not to test hypotheses, and inferential statistics are not required [39]. Descriptive statistics will predominantly be used to summarise participant characteristics and outcome measures. While it is acknowledged that the smaller sample size associated with pilot studies can provide unstable effect size estimates, we intend to carry out some exploratory analyses alongside descriptive statistics for clinician adoption of PCIT, by way of a two-sample *t* test. We will note—but not statistically account for—observed differences between groups at baseline. Measures of variance on this outcome variable will be used to inform the design of a definitive RCT.

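### Adoption is defined against baseline, but the planned t test leaves its outcome unspecified and baseline unadjusted, and the variance kept for sizing the definitive trial is not tied to an analysis

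*Protocol article*

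**What the plan says.** Secondary outcomes defines adoption as the clinician's self-reported number of families seen for PCIT "in the most recent representative 1-week period at 6 months post-randomisation and compared to baseline". Sample size and justification names the same quantity as the envisaged primary outcome of the definitive trial: "number of unique families to whom PCIT was delivered in the most recent representative 1-week period at 6 months post-randomisation, compared to baseline". Table 2 shows the one-week count being collected in both arms at baseline, monthly and at the end of the trial.

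Statistical methods plans "exploratory analyses alongside descriptive statistics for clinician adoption of PCIT, by way of a two-sample *t* test". It then says "We will note—but not statistically account for—observed differences between groups at baseline", and closes with "Measures of variance on this outcome variable will be used to inform the design of a definitive RCT". The last of the Study aims includes "identifying the variability of the proposed primary outcome variable at the end of the intervention, to calculate an appropriate sample size for a definitive RCT".

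The target is stated as "we hope to recruit 10 participants per condition or 20 overall". Allocation is simple 1:1 without restriction (Randomisation and blinding strategies). Clinicians who already carry a full PCIT caseload stay eligible (Inclusion criteria).

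**The concern.** The outcome is stated relative to baseline, the analysis declines to use baseline, and the spread to be carried forward is described as an end-of-intervention quantity. The sections do not fit together on either reading of the t test. If the test compares 6-month counts, it does not estimate the outcome as defined. If it compares changes, it does use each clinician's baseline, which sits badly with the sentence ruling out statistical account of baseline, and an end-of-intervention SD is then not the SD of the variable tested.

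Two things are at stake. The first is the exploratory adoption estimate. Nothing in the allocation balances prior PCIT use, the arms are small, and the 2021 survey quoted in the Background gives a median of 0 (IQR 0 to 1) PCIT clients per week. One or two active users falling in the same arm could dominate the comparison. The second is the sizing of the definitive trial, a stated aim of the pilot, which needs an SD that matches the analysis that trial will use.

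**Working it through.** The plan has no calculated figure to reproduce: 20 clinicians is a pragmatic target, and no alpha, power, effect size, SD or correlation is given.

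**Inputs from the protocol.** 10 per arm; 20% attrition ceiling (Progression criteria), so 10 × 0.8 = 8 per arm completing.

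**Assumptions, for illustration only.** Equal SD at baseline and 6 months; correlation ρ between the two counts from 0 to 0.8; two-sided alpha 0.05; 80% power; a true difference of d = 0.5 of the 6-month SD; normal theory.

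**Step 1: chance imbalance at baseline.** In SD units the difference between arm means has standard error √(2/n).
- n = 10: √0.2 = 0.447; P(|Z| > 0.5/0.447) = P(|Z| > 1.118) = 26%.
- n = 8: √0.25 = 0.5; P(|Z| > 1) = 32%.

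**Step 2: what an imbalance of 0.5 SD does.** The unadjusted 6-month difference shifts by ρ × 0.5 SD: 0.15, 0.25 and 0.35 SD at ρ = 0.3, 0.5 and 0.7. A change-score difference shifts by (ρ − 1) × 0.5 SD: −0.35, −0.25 and −0.15 SD. So analysing change does not remove the problem; adjusting for the baseline count does so under a linear relation.

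**Step 3: which variance the later trial needs.** Relative to the 6-month variance, the factor is 2(1 − ρ) for change and 1 − ρ² for a baseline-adjusted model (ANCOVA). With n per arm = 2(1.96 + 0.84)² × factor / d², the unadjusted 6-month comparison needs 62.8, so 63 per arm. The last column is the power of a change-score analysis in a trial sized at 63 per arm.

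| ρ | Factor, change | n per arm, change | Factor, ANCOVA | n per arm, ANCOVA | Power of change at 63 |
|---|---|---|---|---|---|
| 0 | 2.0 | 126 | 1.00 | 63 | 51% |
| 0.3 | 1.4 | 88 | 0.91 | 58 | 66% |
| 0.5 | 1.0 | 63 | 0.75 | 48 | 80% |
| 0.7 | 0.6 | 38 | 0.51 | 33 | 95% |
| 0.8 | 0.4 | 26 | 0.36 | 23 | 99% |

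The ANCOVA factor never exceeds 1, so the 6-month SD cannot undersize that analysis. The change factor exceeds 1 only for ρ below 0.5. If the SDs differ, that threshold becomes (baseline SD)/(2 × 6-month SD), which is a reason to report both.

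**Step 4: precision of what the pilot can report.** The 95% limits for an SD are √(df/χ²): 0.76 to 1.48 times the estimate at 18 df (20 analysed) and 0.73 to 1.58 at 14 df (16 analysed). An observed ρ of 0.5 in 20 clinicians has a Fisher 95% interval of 0.07 to 0.77. The SD limits are optimistic for a low, skewed count. In simulation at 10 per arm, the nominal 95% interval covered about 85% of the time for a Poisson count with mean 0.5, and about 60% for a negative binomial with mean 0.6 and dispersion 0.5 (both assumed).

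**The case against.** The strongest reply is that an unadjusted two-sample comparison is not an error. Over repeated randomisations it is unbiased. The protocol calls it exploratory, says pilots do not test hypotheses, and concedes that effect estimates will be unstable. Adoption is a secondary outcome and enters none of the progression criteria, which rest on enrolment, attrition and survey response. All of this stands, and it limits the weight of the point. It does not explain why a baseline value that is already collected, and is part of the outcome's own definition, should be ruled out of the analysis.

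A reader might go further and infer that the definitive trial will be sized by inserting the unadjusted end-of-trial SD as it stands. The documents do not say so. The variability is that of the proposed primary outcome, which is itself defined against baseline, so a change-score SD is a possible reading; and the methods section says only that measures of variance will inform the design.

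A reader might also infer that the definitive trial would be underpowered more often than not. Sizing on a point SD does give true power below 80% about 55% of the time, but only if that SD matches the later analysis. If a 6-month SD is used and the trial is analysed by ANCOVA, the chance is P(χ²/df < 1 − ρ²): about 24% to 28% at ρ = 0.5 and 4% to 7% at ρ = 0.7 (18 and 14 df). Whether to size from an upper confidence limit is a trade-off for the later protocol.

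Nor would the pilot fail to yield the parameters needed: baseline and 6-month counts are both collected, so the residual SD and the correlation can be computed. The gap is that the text does not settle which variance applies.

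**Conclusion.** The point holds as a misalignment worth correcting. Adoption is defined against baseline in two sections, while the analysis section neither says what the t test compares nor allows for baseline, and the sizing aim refers to end-of-intervention variability. At 10 per arm there is about a one-in-four chance (nearly one in three at 8 per arm) of a baseline imbalance large enough to move the unadjusted 6-month difference by 0.15 SD or more at ρ = 0.3, and by 0.35 SD or more at ρ = 0.7. The choice of variance can move the later trial's sample size from double to about one third of the figure based on the 6-month SD, over ρ from 0 to 0.8.

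The correlations, equal SDs and normality are assumptions. The probabilities in particular are approximate for a count with many zeros. The consequence is confined to the last study aim, namely the exploratory adoption comparison and the sizing of the definitive trial. Enrolment, completion and the progression criteria are untouched.

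**What to change.** 1. Use one definition of adoption in Study aims, Secondary outcomes, Sample size and justification, and Statistical methods, stating how baseline enters.
2. Replace the t test with an exploratory model of the 6-month count on arm and baseline count, reported as an estimate with a 95% CI. Use an interval suited to a low, skewed count, such as a bootstrap or robust one.
3. Delete the clause that rules out statistical account of baseline differences. Baseline characteristics can still be described by arm.
4. Report the baseline SD, the 6-month SD, the residual SD and the baseline-to-6-month correlation, each with an interval, and state that the definitive trial will be sized on the SD that matches its planned analysis.

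The cost is a few sentences of protocol text and one regression on data already being collected. The downside is the loss of one or two degrees of freedom in a small exploratory analysis.
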